#### Implementation Study

As part of a parallel implementation study, we will identify anticipated challenges to the implementation of the centralized triage process with AI-based risk assessment for CAD. Semistructured interviews and electronic surveys (via REDCap [Research Electronic Data Capture]; Vanderbilt University) will be conducted with key stakeholders—including the catheterization laboratory director, catheterization laboratory manager, catheterization laboratory triage staff, and representation from the CCTA program—at 3 cardiac centers not participating in CarDIA-AI. Survey and interview guides will explore a range of stakeholder perspectives including their awareness of the innovation and attitudes toward the change generally, as well as specific to the innovation, any skills and experiences they might have that could be required in the implementation of the innovation, any concerns about the proposed change, and their intentions to adopt or use the innovation. Development of the survey and interview questions will be informed by the updated Consolidated Framework for Implementation Research, a determinant framework to explain barriers and facilitators to implementation effectiveness [19]. At the participating centers, interviews will be conducted with triage staff to assess their perceptions of the AI model’s success and identify what would be needed to integrate it completely into processes at their site. A list of potential interview and survey questions is available in Multimedia Appendix 6. Descriptive analysis of quantitative survey results (eg, Likert scale responses) will be conducted by the research team. Qualitative analysis of open-ended survey questions and interview transcripts will be carried out using thematic analysis approaches via NVivo software (Lumivero). Data will be coded and mapped to selected constructs of the Consolidated Framework for Implementation Research. Findings will be used to inform the development of strategies and interventions to mitigate identified barriers to the implementation of the centralized triage process if it is determined to be effective. Key barriers will be mapped to the most appropriate implementation strategies from an established compilation of potential strategies, the Expert Recommendations for Implementing Change [20].

### Analyses

#### Statistical Analysis

The primary analysis will compare the proportion of patients referred for cardiac investigation with normal or nonobstructive CAD diagnosed through ICA between the intervention and control groups with a 2-sided *z* test comparing two proportions. All analyses will be carried out according to the intention-to-treat principle; that is, all participants with complete data will be analyzed according to the group to which they were randomized, including noncompliant participants. There are no planned interim analyses. A table of baseline characteristics will summarize patients overall and by randomization arm. Continuous variables will be summarized as mean (SD) or median (IQR), with comparisons between randomization arms made by a 2-sample *t* test (or Wilcoxon rank-sum test if data are not normally distributed). Categorical variables will be summarized as count and percentage, with comparison using the Pearson chi-square test. All statistical analyses will be performed using SAS software (version 9.4; SAS Institute Inc). We will report *P* values up to 3 decimal places and report *P* values less than .001 as <.001. We will use a type I error level of 5%.

We expect a small amount of missing data due to noncompliance and loss to follow-up. As noted above, participants who withdraw will be asked for a reason for withdrawal to determine whether the missing information is random. Participants withdrawing prior to the procedure will be asked whether they intend to proceed to ICA. Finally, we intend to conduct sensitivity analyses based on best- and worst-case scenarios to assess the impact of missing data on the results.

As part of our secondary outcome analysis, we plan to examine whether the intervention can address disparities in ICA findings and evaluate its effects across different sites and eligibility criteria. We will stratify by sex to evaluate whether the intervention reduces the discrepancy in the proportion of normal findings on ICA between male and female patients (female patients are currently 40% more likely to have a normal finding on ICA, meaning female patients are less likely than male patients to experience the therapeutic benefits associated with ICA). Similarly, we also plan to stratify by site to evaluate whether there are differences in the intervention effects between the Hamilton and Niagara sites. To simulate the impacts of using different criteria for CCTA-first eligibility, we will also evaluate the sensitivity of all outcomes to changes to the exclusion criteria, such as incorporating age- and sex-related exclusions. Formal statistical tests will not be used, as we do not anticipate that these hypothesis-generating secondary analyses will be adequately powered.

Given our relatively small sample size, there may be an imbalance at baseline for important covariates. We will therefore undertake an adjusted analysis as a secondary sensitivity analysis, adjusting for age and sex. These covariates were selected based on our external validation study ([name] et al, unpublished paper, April 2025), which found an association between these covariates and the outcome (event rate for male individuals was 71% vs 53% for female individuals, and 68% for those older than 65 years vs 59% for those 65 years and younger).

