#### Informed Consent

Eligible patients are identified by a research assistant and reviewed by a board-certified cardiologist. The research assistant will then contact eligible patients by phone to discuss the study, review the consent form, and obtain verbal informed consent. At the time of the ICA or CCTA, research staff will also obtain written, paper-based consent from patients willing to participate (Multimedia Appendix 2).

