### Outcomes

#### Primary Outcome

The primary outcome is the proportion of normal or nonobstructive CAD diagnosed via ICA, calculated by dividing the number of patients diagnosed with normal or nonobstructive CAD through ICA by the total patients allocated to that arm. This was identified as the most policy-relevant outcome for Ontario Health.

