### Data Collection

#### Overview

All patients will be followed for 90 days from the date of the final diagnostic procedure to capture any relevant outcomes in this stable, elective outpatient population. For patients receiving only ICA or CCTA, this would be the date of the diagnostic procedure; for patients receiving ICA after an initial CCTA, this would be the date of the ICA. All patients will have a CCTA or ICA within 6 weeks of their index referral as per provincial guidelines. Outcomes will be identified at the time one or both procedures (if indicated) are complete. We are allowing an additional 90 days from the final diagnostic procedure to capture any unplanned crossover from CCTA to ICA (see Safety). Follow-up will be done through the provincial CorHealth Ontario Cardiac Registry, housed at the Institute for Clinical Evaluative Sciences. All ICA findings in Ontario are transmitted to the provincial registry via its secure portal. We will extract ICA findings from the registry and derive our outcomes using the standard definition for normal or nonsignificant CAD: <70% stenosis on a major coronary vessel (>2 mm) or <50% stenosis on the left main. For patients who receive CCTA, a cardiologist will manually extract CCTA results from their charts as part of follow-up, as these results are not collected by CorHealth. CCTA findings will be collected in a format and structure that aligns with the CorHealth data collection standards used for ICA findings.

For each CCTA, we will assess the quality of the resulting image. The quality will be graded on a per-patient basis using a 3-class system: low quality, denoting an image in which the coronary anatomy cannot be clearly defined, requiring ICA within 90 days for clarification; suboptimal quality, denoting an image in which the coronary anatomy was equivocal for one or more nonprognostic vessels but not requiring ICA based on CCTA findings and clinical presentation; and high quality, denoting an image in which the coronary anatomy could be clearly defined.

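### The primary proportion is defined over all allocated patients, but the intention-to-treat analysis is limited to participants with complete data, so the primary denominator is not fixed

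*Protocol article*

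**What the plan says.** The Primary Outcome section gives the primary proportion an explicit denominator. It is "calculated by dividing the number of patients diagnosed with normal or nonobstructive CAD through ICA by the total patients allocated to that arm". On that definition, an allocated patient who never has ICA stays in the denominator and is not an event.

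The Statistical Analysis section first states "All analyses will be carried out according to the intention-to-treat principle" and then explains the term: "that is, all participants with complete data will be analyzed according to the group to which they were randomized, including noncompliant participants". Complete data is not defined. The next paragraph adds "We expect a small amount of missing data due to noncompliance and loss to follow-up", and plans best- and worst-case sensitivity analyses for the missing data.

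Three other places bear on the point:

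- Data Collection, Overview: ICA findings are extracted from the registry, and "All ICA findings in Ontario are transmitted to the provincial registry via its secure portal". The same part of the protocol says follow-up needs no direct participant involvement.
- Centralized Triage: intervention patients assessed as low risk receive CCTA first, so many of them have no ICA by design. Participants who withdraw consent after randomization receive usual care.
- Study Design and Informed Consent: the trial is open-label. Verbal consent is taken by phone, and "At the time of the ICA or CCTA, research staff will also obtain written, paper-based consent from patients willing to participate".

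**The concern.** The two sections give different denominators for the same primary estimate. They agree only if no data are missing, and the protocol says some will be. An analysis plan written later cannot satisfy both sentences.

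The difference matters because the outcome is a finding made through ICA, so having no ICA is itself informative. Under the Primary Outcome definition it means no event. Under the Statistical Analysis wording it might mean incomplete data. A CCTA-only intervention patient has an imaging result and is plainly a complete non-event. A control patient who never attends for ICA has no imaging result and could be set aside as incomplete. The same status, no ICA, could then be counted in one arm and dropped in the other.

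The Statistical Analysis section also pulls against itself. It includes noncompliant participants by name, then lists noncompliance as a cause of missing data.

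What is at stake is a primary comparison that partly conditions on what happens after open-label allocation, with the choice of denominator still open when the data are seen.

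**Working it through.** **Inputs.** Sample Size section: 44% control, 22% intervention; 200 patients before inflation; noncompliance up to 5% in both arms (factor 1.23); loss to follow-up up to 2%; 126 per arm. Statistical Analysis section: two-sided z test, 5% type I error. Missingness patterns and the 32% rate used below are assumptions.

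**Step 1: the plan's own figures.** With n per arm, d = p1 − p2 and p̄ = (p1 + p2)/2, power = Φ{[d√n − 1.96√(2p̄(1 − p̄))] / √(p1(1 − p1) + p2(1 − p2))}.

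- n = 100, 44% vs 22%: (2.200 − 1.303)/0.647 = 1.387, power 91.7% (stated 91.9%).
- n = 100, 44% vs 25%: (1.900 − 1.318)/0.659 = 0.884, power 81.2% (stated 81.3%).
- Noncompliance: 1/(1 − 0.05 − 0.05)² = 1.235; 200 × 1.23 = 246. Loss: 246/0.98 = 251.02, taken up to 252.

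The figures reproduce. The factor of 1.23 matches a dilution factor, which keeps noncompliant patients in the analysis. Only the 2% is handled as loss of patients.

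**Step 2: the two denominators.** Let p be the event rate among completers and m the share of an arm with missing data. The complete-data estimate is p. The all-allocated estimate, with missing patients counted as non-events, is p(1 − m).

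| Missing | All-allocated difference | Complete data |
|---|---|---|
| 2% in both arms | 0.44 × 0.98 − 0.22 × 0.98 = 21.6 points | 22.0 |
| 7% in both arms | 0.44 × 0.93 − 0.22 × 0.93 = 20.5 points | 22.0 |
| 7% in control only | 0.44 × 0.93 − 0.22 = 18.9 points | 22.0 |
| 7% in intervention only | 0.44 − 0.22 × 0.93 = 23.5 points | 22.0 |

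For scale, the standard error of the difference at 126 per arm is √(0.44 × 0.56/126 + 0.22 × 0.78/126) = 5.8 points. The largest shift in the table, 22.0 − 18.9 = 3.1 points, is about half of that.

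**Step 3: effect on the test.** Pooled z tests on whole patients, with 9 of 126 (7.1%) missing in one arm:

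| Completer rates | Missing | Complete data | All allocated |
|---|---|---|---|
| 44% vs 22% | 9 control | 51/117 vs 28/126: 21.4 points, p = 0.0004 | 51/126 vs 28/126: 18.3 points, p = 0.0018 |
| 44% vs 32% | 9 control | 51/117 vs 40/126: 11.8 points, p = 0.057 | 51/126 vs 40/126: 8.7 points, p = 0.149 |
| 44% vs 32% | 9 intervention | 55/126 vs 37/117: 12.0 points, p = 0.053 | 55/126 vs 37/126: 14.3 points, p = 0.019 |

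At the planned effect the conclusion is the same either way. At the assumed smaller effect the last row crosses 5%.

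**Step 4: power at 44% vs 22%.** With 2% missing in both arms it is 96.1% for complete data and 96.0% for all allocated. With 7% it is 95.2% and 94.5%. The denominator is not a sample-size problem.

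**The case against.** The strongest reply is that the Statistical Analysis wording can be read consistently with the Primary Outcome definition. Noncompliant participants are kept by name, and the registry records every Ontario ICA. A patient with no registry ICA can therefore be said to have complete data and to be a non-event. Expected missingness is small, reasons for withdrawal are logged, and best- and worst-case analyses are planned. Detailed missing-data rules also commonly sit in an analysis plan that is not shown here.

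Much of this stands, and it rules out several stronger readings that a reader might infer:

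- That a patient with no ICA is certain to be dropped. The text does not say so; complete data is undefined, and exclusion is only a natural reading.
- That the error favors the intervention. It does when losses are equal or fall mainly in the control arm; it reverses when they fall mainly in the intervention arm.
- That the allowances of 5% and 2% add up to 7% with no ICA in each arm. The 5% is handled as dilution, nothing equates noncompliance with no ICA, and CCTA-only patients have no ICA by design. The 7% rows above are illustrations only.
- That patients who do not sign at the procedure are removed from the analysis. Verbal consent comes first, Ethical Considerations allows documented consent before or at the procedure, and no passage states such a removal.

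What the reply does not answer is the conflict itself. The protocol limits the analysis to complete data and names noncompliance as a cause of missing data, which sits badly with the registry-based reading. The best- and worst-case analyses bound the effect of missing data, but they do not say which estimate is primary or when having no ICA counts as missing.

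**Conclusion.** The concern holds as a conflict between two stated denominators for the primary outcome, and it should be fixed. The likely effect is small: 0.4 points if only the plan's 2% loss allowance applies equally to both arms. One-sided missingness of 7% would move the difference down by 3.1 points or up by 1.5, depending on the arm. These figures assume completer rates of 44% and 22% and count missing patients as non-events. The missingness patterns are not taken from the documents.

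The conclusion is stable at the planned 22-point effect. Only at a smaller effect, such as the assumed 44% vs 32%, could the choice of denominator decide significance. The documents support neither a fixed direction of bias nor certain exclusion of patients without ICA.

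**What to change.** 1. In Statistical Analysis, replace the restriction to participants with complete data by all randomized participants, matching the Primary Outcome section.
2. Take ICA status and findings from the registry for everyone whose linkage is permitted, including noncompliant and withdrawn patients. This matters for intervention-arm withdrawals, who return to usual care and so may have an ICA event.
3. Count no registry ICA within the outcome window as a non-event. State when the window starts for a patient with no procedure, because follow-up is currently dated from the final diagnostic procedure.
4. Treat as missing only patients whose linkage is refused or fails. Keep them in the all-allocated denominator as non-events in the primary estimate, and vary that assumption by arm with the planned best- and worst-case analyses. Counting them as non-events is a convention and can help either arm, so those analyses should be reported beside the primary result.
5. Report the complete-data analysis as a sensitivity analysis, and remove noncompliance as a cause of missing primary-outcome data.

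The cost is wording in the protocol and analysis plan. The registry extract is already planned, and the sample size stays at 252. The reported effect may become slightly less favorable.

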#### Economic Analysis

For the budget impact analysis, we will use the trial data and Ontario Health Insurance Program professional and technical fees to compare the procedural costs of screening with usual care (cost of ICA) and the AI model (weighted average of the cost of ICA and the cost of CCTA based on the AI model recommendation and CCTA output). A catheterization laboratory cost, which is not included in Ontario Health Insurance Program fees, will be added to the cost of ICA. In a secondary economic analysis, the 90-day health care expenditures post index investigation (eg, revascularization and hospitalization) will be derived using the Institute for Clinical Evaluative Science databases and compared between the 2 diagnostic strategies. Bootstrap techniques will be used to deal with sampling uncertainty and calculate 95% CIs around the costs [21]. The per-patient costs will be extrapolated to Ontario and Canada to document the health care cost savings at the population level.

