To obtain the input data for the tool, a research assistant will manually review the ICA referral forms of eligible patients and associated documentation in their chart (Figure S1 in Multimedia Appendix 3). If there are ambiguities or inconsistencies in the referral form or chart, these data will be managed based on predetermined standard operating procedures (Multimedia Appendix 5). Missing data will be imputed. Any ambiguities or inconsistencies requiring clinical interpretation will be treated as missing and imputed.

The user interface of the AI tool consists of various input fields that correspond to the model predictors (Figure S2 in Multimedia Appendix 3). Users either manually enter a value (eg, for Age) or select a value from the field drop-down menu (eg, for Referral Month). The input fields largely reflect nominal, structured data elements on the referral forms completed by referring physicians. While clinical expertise is not required to use the tool, study personnel using the tool have discussed the contents of the form at length with members of the Heart Investigation Unit in preparation for the trial.

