#### Secondary Outcomes

Secondary outcomes include (1) the number of angiograms avoided, (2) deviation from management recommendations following CCTA (ie, angiograms performed when not recommended), (3) the diagnostic yield of ICA (ie, number of patients diagnosed with obstructive CAD out of all patients undergoing ICA), (4) the number of low-quality CCTAs, (5) the difference in the proportion of normal or nonobstructive CAD diagnosed through ICA between male and female patients; and (6) the difference in the proportion of normal or nonobstructive CAD diagnosed through ICA between sites. Furthermore, we will assess the budget impact of the AI intervention.

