### Safety

Both CCTA and ICA are considered standard of care in the patient population for CarDIA-AI. A total of 50% (126/252) of patients (control arm) will automatically receive usual care. Patients randomized to the intervention who receive a recommendation to proceed directly to ICA will effectively also receive usual care. Patients who receive a recommendation to proceed to CCTA will not be at increased risk of missed diagnosis, as CCTA has been found to be as effective as ICA in both diagnosing and ruling out obstructive CAD in stable outpatients [9,22-24]. A potential harm in the intervention group is double testing, which would occur when the CCTA is of poor quality and the degree of obstructive CAD cannot be clearly quantified. Double testing may also occur when the AI model predicts a low probability of obstructive CAD, and in turn, recommends CCTA, but the CCTA is positive and the patient requires confirmatory or therapeutic ICA. Both of these potential harms are only expected to occur in a small number of patients, and the risk in the intervention group will be much lower as compared to usual care. We will also track ICA within 90 days of the last imaging procedure to ensure that there are no events in the intervention group representing unplanned crossover.

In terms of potential model performance errors, the data quality committee will periodically monitor the performance of the model, with particular attention to when the model appears to be performing outside its normal parameters. No formal auditing is planned.

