### Conclusions

The CarDIA-AI trial is the first to leverage AI for the triage of patients referred for assessment of suspected CAD. If successful, the intervention could optimize the referral process, resulting in millions of dollars in cost savings to the health care system while improving the patient experience by reducing exposure to unnecessary procedural risks.

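### The budget impact analysis leaves out the cost of the AI triage itself, and its weighted-average wording does not settle whether patients with both tests are charged for both

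*Protocol article*

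**What the plan says.** All references are to the protocol article.

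- **Aim.** Secondary Outcomes closes with the statement that "we will assess the budget impact of the AI intervention".
- **Cost sources.** Economic Analysis: "we will use the trial data and Ontario Health Insurance Program professional and technical fees".
- **Comparison.** These are used to "compare the procedural costs of screening with usual care (cost of ICA") on one side, and on the other "the AI model (weighted average of the cost of ICA and the cost of CCTA based on the AI model recommendation and CCTA output").
- **One addition to the fees.** "A catheterization laboratory cost, which is not included in Ontario Health Insurance Program fees, will be added to the cost of ICA".
- **Secondary economic analysis.** It covers 90-day spending after the index investigation, with revascularization and hospitalization as examples.
- **Use of the result.** Per-patient costs are extrapolated to Ontario and Canada as savings. The Conclusions section speaks, conditionally on success, of the intervention "resulting in millions of dollars in cost savings to the health care system".
- **What the intervention consumes.** Under AI-Based Risk Assessment for Significant CAD, "a research assistant will manually review the ICA referral forms of eligible patients and associated documentation in their chart" to supply a model with 42 predictors. The Setting section places the tool on a dedicated virtual machine in a hospital research data center.
- **Two-test patients.** Centralized Triage sends low-risk patients to CCTA and then to ICA where appropriate. Safety names two routes to double testing: a poor-quality CCTA, and a low predicted probability where "the CCTA is positive and the patient requires confirmatory or therapeutic ICA".

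**The concern.** The quantity promised and the quantity costed differ. The promise concerns the intervention, which is an AI tool run inside a triage process. The listed components are imaging procedures only. Staff time, hosting and maintenance arise only because the intervention exists, so leaving them out lowers the cost of one arm and not the other.

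The second issue is wording. The pathway has three cost states: direct ICA, CCTA alone, and CCTA followed by ICA. An average of two unit costs describes two states. Whether the third is charged in full depends on what the weights are, and the article does not say.

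The economic result is secondary and does not touch the primary analysis. It is, however, meant to be multiplied up to a province and a country, so any error per patient scales with it.

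**Working it through.** **No figure to reproduce.** The article gives no unit cost, no expected share sent to CCTA, no double-test rate and no saving. The check is therefore algebra, followed by an illustration on assumed inputs.

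**Notation.** I = cost of an ICA including the laboratory cost; C = cost of a CCTA; q = share of the intervention arm sent to CCTA; d = share of those who go on to ICA; T = triage cost per intervention patient.

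**1. Triage cost**

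- Full cost per intervention patient = (1 − q)I + qC + qdI + T.
- Usual care = I.
- Full saving = q[(1 − d)I − C] − T.
- Saving with triage unpriced = q[(1 − d)I − C].
- Difference = T, whatever q, d, I and C are. Scaled to N referrals it is N × T.

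The 90-day analysis does not repair this, because it starts after the index investigation and triage comes before it.

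In the trial the tool is also run for control patients, according to Usual Care. That is a feature of the study and not of usual care, so T belongs to the intervention arm alone.

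**2. Double testing (T set aside)**

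The shares of patients receiving ICA and CCTA are (1 − q + qd) and q. They sum to 1 + qd. Three readings of the weighted average follow.

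| Reading | Intervention-arm cost | Shortfall |
|---|---|---|
| Weights are the shares receiving each test | (1 − q + qd)I + qC | 0 |
| One final test per patient, taken from the CCTA result | (1 − q + qd)I + q(1 − d)C | qdC |
| Weights from the AI recommendation only | (1 − q)I + qC | qdI |

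The third reading ignores the CCTA result, which the sentence expressly uses, so it fits the text poorly. The first two both fit.

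**3. Illustration, all inputs assumed.** Take I = 1, C = 0.4, q = 0.5, d = 0.2.

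- Shares reading: 0.6 + 0.5 × 0.4 = 0.80, saving 0.20.
- Final-test reading: 0.6 + 0.5 × 0.8 × 0.4 = 0.76, saving 0.24, overstated by 0.04/0.20 = 20%.
- Recommendation-only reading: 0.5 + 0.5 × 0.4 = 0.70, saving 0.30, overstated by 0.10/0.20 = 50%.

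The relative overstatement does not depend on q. It is dC/[(1 − d)I − C] for the final-test reading and dI/[(1 − d)I − C] for the recommendation-only reading. Over C = 0.2 to 0.4 and d = 0.1 to 0.4, still with I = 1:

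- final-test reading: from 0.02/0.70 = 3% to 0.16/0.20 = 80%;
- recommendation-only reading: from 0.10/0.70 = 14% to 0.40/0.20 = 200%;
- shares reading: 0 throughout.

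The width of these ranges shows that the wording needs settling. It does not estimate what this trial will find.

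**The case against.** **On double testing.** A reader might infer that the formula cannot accommodate patients with both tests, and hence that savings are certainly overstated. The article does not support that. The weights depend on the CCTA result as well as the AI recommendation, and the CCTA result is what sends a patient on to ICA. Trial data are used, costs are described per patient and bootstrapped, and ICA after CCTA is captured in follow-up. A loosely worded expected cost over the three pathways is a fair reading, and under it the error is zero. The Safety section also expects double testing in only a small number of patients. This objection stands in full against the stronger inference. What remains is that the sentence also admits a reading that loses a cost.

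**On triage cost.** The comparison is labelled procedural, so the omission can be called a declared limit of scope. Abstraction by a research assistant may not represent routine operation, and Future Directions leaves use by triage staff to later studies. A fuller protocol or health-economic plan may list more components. The savings language is conditional and is not presented as an output of this formula.

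Parts of this stand: trial staff time is an imperfect proxy, which argues for a range instead of a single figure. The scope label does not settle the matter, because the same result is described as the budget impact of the intervention and scaled to population savings. The analysis also already steps outside the fee schedule to add a laboratory cost to ICA. That addition is legitimate, but it raises the apparent saving, while the intervention's own cost, which would lower it, is not listed. The point rests on the components the article does state, not on detail it left elsewhere.

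**Conclusion.** The point holds in two parts of unequal strength.

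- **Triage cost: holds.** With the components as listed, the per-patient saving is too high by T under every reading of the weighted average, and the population figure by T times the number of referrals. T is not in the article, so no percentage can be given. The direction is certain provided T is above zero, which the described staff review and hosting imply.
- **Double testing: conditional.** The overstatement is zero if the weights are the shares receiving each test. It is qdC if each patient is counted under one final test. The documents do not say which. The illustrative percentages rest wholly on assumed unit costs and double-test rates. A claim that savings are overstated through double testing goes further than the text allows.

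The consequence is confined to the economic outcome and the savings statements that may be drawn from it.

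**What to change.** In Economic Analysis, before the data are analyzed:

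1. Replace the weighted-average sentence with a patient-level definition: each randomized patient's cost is the sum of all tests actually received, with CCTA and ICA both charged when both are done.
2. Add a triage cost per referral (abstraction time, hosting, upkeep) to every intervention-arm patient and to no control patient. Give a sensitivity range, since research-assistant time may differ from routine staffing.
3. Bootstrap these patient-level costs.
4. Report the saving extrapolated to Ontario and Canada with and without the triage cost.

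If triage is not to be priced, the alternative is to label the result as a comparison of procedural cost only and to limit the savings claim to that.

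The cost is a change of wording plus an estimate of staff time and hosting. The price to the investigators is a somewhat less favorable saving. No trial procedure changes.
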